### **Collaborating researchers:**

[name] [name], PhD. Department of Pharmacology and Pediatrics, Faculty of Medicine, Malaga University. Biomedical Research Institute of Malaga (IBIMA), Malaga, Spain. Unit of Pediatric Pulmonology, Malaga Regional Hospital, Malaga, Spain.

[name] [name]. Physiotherapist specialist in children chest physiotherapy. Department of Pharmacology and Pediatrics, Faculty of Medicine, Malaga University, Biomedical Research Institute of Malaga (IBIMA), Malaga, Spain.

[name] [name]. Professional musician and music teacher of children. Department of Pharmacology and Pediatrics, Faculty of Medicine, Malaga University. Biomedical Research Institute of Malaga (IBIMA), Malaga, Spain. Department of Education. Andalusian Government, Malaga, Spain.

**Objective:** To develop a strategy based on music therapy as adjunct to daily chest physiotherapy in children with cystic fibrosis and to evaluate its effects.

**Study design:** Interventional - randomized controlled trial. Single center: Unit of Pediatric Pulmonology, Malaga Regional Hospital.

**Disease or disorder under study:** Cystic fibrosis.

**Participants:** Children between ages of 2-17 from the Pediatric Pulmonology Unit at Malaga Regional Hospital. The sample size determined in each group is 13 participants. A total of 39 participants are necessary.

**Total study period:** Two years.

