**- Sample size:**

To calculate the sample size, the perception of time taken to complete the routine has been assumed as main variable. According to Grasso et al, (2000) where the control group values in this variable were  $0.2 \pm 10.2$  (mean  $\pm$  SD), considering these values as baseline, a power of 80 %, a confidence level of 95 %, and a similar variability at the end of the study, a difference of 8 minutes would be considered as statistically significant with a sample size of 13 subjects. A total of 39 participants are necessary.

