**- Randomization:**

After providing written informed consent, a random allocation sequence will be carried out using the Epidat program. The participants will be randomly allocated into intervention group, control group without music, or control group with music.

The groups are the followed:

- Intervention group or TG (participants that use specific composed music as an adjunct to chest physiotherapy routine).
- Control group without music or CG (participants that do not use music as an adjunct to chest physiotherapy routine).
- Control group with music or PG (participants that use commercial music as an adjunct to chest physiotherapy routine).

Participants in every group will continue with their usual treatment regimen without modifications.

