#### **- Statistical analysis:**

Statistical analysis will be performed using SPSS Software.

Initially a descriptive analysis of the study variables will be carried out, the values of the continuous variables will be summarized in a table where their corresponding means and standard deviation will be shown. The categorical variables will be presented in absolute and relative frequencies.

To compare qualitative measures Chi-square or Fisher tests will be used, and ANOVA or Kruskal-Wallis tests to quantitative.

To contrast the differences in the evolution of the variables between the different groups the multivariate analysis of variance test of repeated measures (MANOVA) will be applied with a factor between subjects (group) and a factor intra subjects (different moments of the intervention). Depending on the compliance of the sphericity condition, the Greenhouse-Geisser correction will be used. To contrast the differences between baseline and final measures in each group Wilcoxon test will be applied. To compare response to using music after the intervention into TG and PG, Mann–Whitney U test was used.

To compare response to using music after the intervention into TG and PG, Mann–Whitney U test will be used.

A significance of 5% ( $p < 0.05$ ) will be required to consider a difference as statistically significant.

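### No pairwise between-arm contrast is planned for the main variable; the only arm-by-arm analysis is an ungated before/after Wilcoxon test in each group

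*Combined protocol and SAP*

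**What the plan says.** All the tests are in the Statistical analysis section of the combined protocol and SAP.

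- **Between arms, omnibus.** Quantitative measures are compared by ANOVA or Kruskal-Wallis. Change over time is compared by a repeated-measures MANOVA with group and time as factors. With three arms, each of these tests whether some arm differs. No follow-up contrast is named.
- **Between arms, pairwise.** There is one such test, a Mann-Whitney U: "To compare response to using music after the intervention into TG and PG". It concerns liking of the music and leaves out the no-music arm (CG).
- **Within arm.** "To contrast the differences between baseline and final measures in each group Wilcoxon test will be applied".
- **Threshold.** The same 5% level applies to every test. There is no order of testing, and no statement of which result supports which conclusion.

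Under Randomization, "The participants will be randomly allocated into intervention group, control group without music, or control group with music". Under Sample size, "the perception of time taken to complete the routine has been assumed as main variable". The Statistical analysis section speaks of the study variables in general and ties no test to this one, so I read the general wording as applying to it.

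**The concern.** The hypothesis sets composed music (TG) against commercial music (PG) and no music (CG). A significant omnibus result does not say which arm differs, and the next analysis in the plan that yields a result for each arm is the set of three Wilcoxon tests. A report could therefore say that perceived time fell significantly with composed music but not without music, and present this as an effect of the music. That pattern does not test TG against CG. Two arms with the same true change can easily fall on opposite sides of p = 0.05, especially at 13 per arm.

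Shared change is credible here. Families know whether they are using music, the outcomes are self-reported, and the same questionnaire is completed three times. What is at stake is the trial's central conclusion about which arm, if any, does better.

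**Working it through.** **The plan's own figure.** Inputs from Sample size: SD 10.2, "a power of 80 %, a confidence level of 95" %, and "a difference of 8 minutes would be considered as statistically significant with a sample size of 13 subjects". Two-sided testing is assumed.

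- Before/after formula: n = (SD × (1.960 + 0.842) / difference)² = (10.2 × 2.802 / 8)² = 12.76, rounded up to 13. This matches.
- Two-arm formula: n per arm = 2 × 12.76 = 25.5, rounded up to 26. This does not match.

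The stated 13 is thus what a within-arm comparison would need on these inputs, taking 10.2 as the SD of change.

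**How often equal arms look different.** Three arms of 13 were simulated with the same true mean change in each (normal changes, SD 10.2, 200,000 trials per scenario). Each arm was tested by an exact two-sided Wilcoxon signed-rank test at 0.05. The text does not say whether 10.2 is the SD of a level or of a change. If it is a level, with "a similar variability at the end of the study", a baseline-to-final correlation of 0.5 gives the same SD of change: 10.2 × √(2 × (1 − 0.5)) = 10.2.

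Let p be the chance that one arm's Wilcoxon test is significant. The arms are independent, so:

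- TG significant, at least one control not: p(1 − p²)
- TG significant, both controls not: p(1 − p)²
- any disagreement among the three arms: 1 − p³ − (1 − p)³

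| Shared change (min) | p (simulated) | TG significant, at least one control not | TG significant, both controls not | Any disagreement |
|---|---|---|---|---|
| 0 | 0.047 | 5% | 4% | 13% |
| 4 | 0.243 | 23% | 14% | 55% |
| 6 | 0.475 | 37% | 13% | 75% |
| 8 | 0.713 | 35% | 6% | 61% |

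Example at 6 minutes: 0.475 × (1 − 0.475²) = 0.475 × 0.774 = 0.37, and 0.475 × 0.525² = 0.13.

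**The planned omnibus test.** A one-way ANOVA on the changes, standing in for the group-by-time term of the MANOVA, is significant in 5% of trials in every row. If the Wilcoxon tests are read only when it is significant, the third column falls to 2.1%, 2.4% and 2.5% at 4, 6 and 8 minutes (40,000 trials), and is lower still at 0.

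**Power of the missing contrast.** For two arms of 13, the standard error is 10.2 × √(2/13) = 4.00, so an 8-minute difference is 2.00 standard errors. Power is 0.52 by normal approximation and 0.48 by t-test at two-sided 0.05. At 0.025, the stricter level when two contrasts are adjusted, the normal approximation gives 0.40.

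**The case against.** The strongest reply is that each test has its own stated purpose. The between-group question goes to the MANOVA, which uses the randomised comparison and keeps its 5% error rate. The Wilcoxon test is given only the baseline-to-final question. Nothing says that an arm effect will be claimed from it. This stands, and it rules out some stronger readings:

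- A reader might infer that the plan has no between-arm comparison or discards the randomisation. It does neither.
- A reader might infer that the sponsor intends to compare p-values across arms. The text does not say so. The match between 13 and the before/after formula fits such reliance but does not prove it.
- A reader might take the 75% disagreement rate as a false-claim rate. It includes patterns unfavourable to composed music. The clearest false pattern, TG significant and both controls not, peaks at about 14%.

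The size of any shared change is also an assumption. The control value cited under Sample size is 0.2 ± 10.2. If that is a change score, the only cited control evidence suggests almost no shared change, and the 0-minute row applies.

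What the reply leaves open is the follow-up step. The plan does not make the Wilcoxon tests depend on the omnibus result. Even if it did, that protects only when all three arms are equal; when one arm does differ, within-arm tests still do not show which.

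**Conclusion.** The point holds as an omission with a specific consequence. The omnibus comparison is sound, but no planned analysis of the main variable compares TG with CG or TG with PG, and the only arm-by-arm results come from within-arm tests at p < 0.05 with no rule for reading them. If those tests are used to name the arm that worked, the false pattern of TG significant with at least one control not arises in 5% to 37% of trials for shared changes of 0 to 8 minutes. If they are read only after a significant omnibus test, it is about 2.5% or less. Both ends should be shown, because the plan does not say which reading applies.

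These rates assume two-sided tests, normal changes with SD 10.2, no dropout, and the quantitative perceived-time item as the main variable.

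**What to change.** In the Statistical analysis section:

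1. Keep the repeated-measures MANOVA as the overall comparison.
2. Add two prespecified contrasts on perceived time at 12 weeks, TG minus CG and TG minus PG, as baseline-adjusted differences (ANCOVA) with 95% confidence intervals.
3. Adjust these two for multiplicity, for example by Holm. Treat the same contrasts on other outcomes as exploratory.
4. Keep the within-group Wilcoxon results as descriptive only.
5. State that any claim of an arm effect rests on the between-arm contrasts.

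The data and software stay the same, and the extra analysis work is small. The real cost is candour about precision: at "The sample size determined in each group is 13 participants. A total of 39 participants are necessary", power for an 8-minute pairwise difference is about 0.48 without baseline adjustment or multiplicity control, and the plan should say so. For 80% power the unadjusted comparison needs 26 per arm, or 31 with Bonferroni for two contrasts. Baseline adjustment helps if 10.2 is the SD of a single measurement: 24, 20 or 14 per arm for an assumed correlation of 0.3, 0.5 or 0.7 (single contrast at 0.05). The documents do not give that correlation.

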## HYPOTHESIS

The adherence in chronic disease treatment is very low (Sabaté, 2003), being the CPT adherence in CF less than 50 % (Goodfellow et al, 2015). To improve airway clearance in CF patients, there is no therapeutic alternative to CPT, in any case, it has to be combined with physical exercise (Kriemler et al, 2016). Motivation is the best way to optimize treatment adherence (Smith et al, 2010) and the use of carefully selected music during CPT (Grasso et al, 2000) or physical exercise (Calik-Kutukcu et al, 2016) in CF

patients can lead to a positive affective response that could be translated into a improvement in adherence (Smith et al, 2010) and therefore in airway clearance that could maintain the lung function and improve the children's and family member's quality of life.

Baseline hypothesis: Significant differences are expected in chest physiotherapy enjoyment and perception, adherence to daily chest physiotherapy, pulmonary symptomatology and quality of life between participants that use specific composed music as an adjunct to chest physiotherapy routine (intervention group), commercial music as an adjunct to chest physiotherapy routine (control group with music), or no music (control group without music).

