**- Data collection:**

Demographic and clinical data will be collected in the case report formulary from each participant (Annex). Specifically: age, gender and respiratory infection exacerbations that requiring hospitalization.

These participants are controlled in the Pediatric Pulmonology Unit at Malaga Regional Hospital, where each child with cystic fibrosis has a detailed clinic history, being the clinical variables systematically included and the treatment updated. Therefore, the present study does not imply additional clinic information collection. Demographic and clinical information will be completed by Pediatricians during the usual follow-up.

In addition, participants will complete a baseline and 2 evaluation questionnaires during the trial-period in order to know children's and family members' chest physiotherapy perception. The questionnaires will be conducted about chest physiotherapy experiences to evaluate the evolution of their perceptions during the trial-period. These questionnaires are designed specifically to know evolution of CPT characteristics such as, enjoyment and perception or time or adherence to daily chest physiotherapy, after the use of music therapy as an adjunct to CPT (Grasso et al, 2000). The perception of pulmonary symptomatology and the impact on the quality of life will be also evaluate using a visual analog scale (VAS) to assess the magnitude of dyspnea in pulmonary diseases such as CF (Bausewein et al, 2007) and the revised cystic fibrosis quality of life questionnaire (Quittner et al, 2000), respectively.

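### One 5% rule covers about 18 outcomes in three arms with no primary outcome, contrast or time point in the analysis, so a single significant item cannot be read as confirmatory

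*Combined protocol and SAP*

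**What the plan says.** The document is a combined protocol and SAP.

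- **Statistical analysis.** The section lists Chi-square or Fisher tests, ANOVA or Kruskal-Wallis tests, a repeated-measures MANOVA with group and time factors, Wilcoxon tests of baseline against final in each arm, and a Mann–Whitney test of the response to music in TG against PG. It closes with one rule: 5% "will be required to consider a difference as statistically significant". The only correction mentioned is Greenhouse-Geisser, which deals with sphericity and not with the number of tests.
- **Hypothesis.** "Significant differences are expected in chest physiotherapy enjoyment and perception, adherence to daily chest physiotherapy, pulmonary symptomatology and quality of life" among the three groups. None of these domains is ranked above another, and the objectives do not rank them either.
- **Sample size.** Here "the perception of time taken to complete the routine has been assumed as main variable". The calculation uses "a power of 80 %, a confidence level of 95" per cent, and concludes that "a difference of 8 minutes would be considered as statistically significant with a sample size of 13 subjects". The main variable is not mentioned again in the analysis section.
- **Study variables.** Perception of time has two items: a yes/no item on whether the routine feels long, and a quantitative item on how much time it seems to take.
- **Design.** "The participants will be randomly allocated into intervention group, control group without music, or control group with music", and "participants will complete a baseline and 2 evaluation questionnaires during the trial-period", so there are follow-ups at 6 and 12 weeks.

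**The concern.** A 5% threshold limits the false-positive risk of one test. When it is applied to many outcomes with equal standing, the chance that at least one crosses it by luck is far above 5%. This plan does not say beforehand which result would count as the answer. The outcome, the pair of arms and the visit are all left open in the analysis.

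At stake is the status of the conclusion. The applicability section anticipates improvement across the same domains and direct use in healthcare practice. If one symptom item or one adherence item came out at p<0.05, the plan would give a reader no means of telling a confirmed effect from the chance finding that such a set of tests is expected to produce.

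**Working it through.** **1. The plan's own figure.** Inputs from the sample size section: difference 8 minutes, SD 10.2, power 80%, confidence 95% (two-sided assumed; the plan does not say).

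- One-sample or paired formula: n = [10.2 × (1.960 + 0.842) / 8]² = 12.76, rounded up to 13. This reproduces the stated 13.
- Two-sample formula: n per arm = 2 × 12.76 = 25.5, rounded up to 26. This does not reproduce it.

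Step 5 uses this result.

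**2. Outcomes compared among arms** (study variables section):

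| Domain | Items |
|---|---|
| Hospitalised exacerbations (number, days) | 2 |
| Adherence | 4 |
| Attitude | 2 |
| Perception of time | 2 |
| Dyspnoea scale | 1 |
| Respiratory symptoms (day cough, night cough, expectoration, its type, breathing difficulty, whistling, congestion) | 7 |
| **Total** | **18** |

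The two accompanying-activity items and the five music items are left out.

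**3. One three-arm test per outcome at 5%, no true effect, independent outcomes.**

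- Chance of at least one false positive: 1 − 0.95^18 = 0.603, or 60%.
- Expected number of false positives: 18 × 0.05 = 0.9.

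**4. Correlated outcomes.** The documents give no correlations, so these are assumptions. The simulation used null trials with 13 per arm, three arms, 18 equally correlated normal outcomes and one F-test each.

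| Assumed correlation | At least one false positive |
|---|---|
| 0 | 60% |
| 0.3 | about 52% |
| 0.5 | about 41% |
| 0.7 | about 30% |

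Repeat runs move these figures by about one percentage point. Fisher tests on 13 per arm are conservative and would lower them somewhat. The planned group-by-time tests and within-arm Wilcoxon tests are not counted and add further chances.

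**5. Power of a single confirmatory contrast at 13 per arm.**

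- Standard error = 10.2 × √(2/13) = 4.00, and 8 / 4.00 = 2.00.
- Power = Φ(2.00 − 1.96) = 52% by the normal approximation, and 48% by the t-test.
- If alpha were split over three pairwise contrasts (0.05 / 3 = 0.0167), power would be about 35% (normal) or 30% (t-test).

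**The case against.** The plan is not silent on priority. It names a main variable. It also points towards the end of the study, because the sample size section assumes similar variability at that point and the Wilcoxon tests compare baseline with final. This stands in part: it makes the final questionnaire the natural choice. It does not answer the concern, because neither place declares a primary analysis, the analysis section does not use the main variable, that variable covers two items, and no pair of arms is singled out.

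Independence is also unrealistic. Most symptom items come from one questionnaire and the adherence items describe one routine, so 60% is the upper end for one three-arm test per outcome. This stands, and is why a range is given. Even 30% is six times the nominal 5%.

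A reader might infer several stronger things that the documents do not support:

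- **That every outcome is tested separately at every visit, making a very long list of p-values.** The section assigns no visit to the simple group comparisons and handles the visits jointly in the repeated-measures model. The case report form records hospitalisations once for the whole study period.
- **That all three pairs of arms are tested on each outcome.** No such comparisons are prescribed.
- **That the five music items belong in the same count.** The analysis section names a specific test for only one of them, between TG and PG.
- **That any one significant item is declared to prove the hypothesis.** No such success rule is written, and the hypothesis joins its domains with an and.
- **That a positive result would carry almost no information.** That goes too far. It would be a lead, but not a confirmation.

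Finally, the within-arm Wilcoxon tests address change over time, which is a different null hypothesis from no difference between arms. They are therefore kept out of the calculation.

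**Conclusion.** The concern holds in this form: the plan applies an uncorrected 5% rule to about 18 outcomes in three arms and identifies no confirmatory analysis. Under no effect, with one three-arm test per outcome, the chance of at least one false positive lies between about 30% (correlation 0.7) and 60% (independence). The range rests on the count of 18, on the assumed equal correlations, and on normal-theory tests at 13 per arm.

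The trial remains runnable and its data remain useful. What is missing is protection of its claims, and the plan should supply it. The main variable already chosen for sizing makes this easy. The mismatch between 13 per arm and a between-arm comparison is a separate issue and matters here only as a cost of the remedy.

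**What to change.** Make these changes before any outcome data are seen; a primary analysis chosen afterwards would not be credible.

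1. **Statistical analysis section.** State that the only confirmatory analysis is the quantitative perceived-time item (the minutes variable behind the sample size), TG against CG, at the final 12-week questionnaire, two-sided 5%.
2. **Fixed sequence.** Only if that test is significant, test TG against PG on the same variable and visit at 5%. This controls the family-wise error for the two claims without splitting alpha.
3. **Everything else.** Report all other outcomes, the 6-week results and the within-arm comparisons as estimates with 95% confidence intervals, labelled exploratory. The 5% rule should no longer apply to them.
4. **Hypothesis section.** Say that only the perceived-time variable can confirm the hypothesis.

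**Cost.** The change is to the text; no additional data are needed. Fewer results can be called significant, and the conclusion would rest on a test with about 48–52% power for 8 minutes at SD 10.2 with 13 per arm, not the 80% stated. The second step can succeed only if the first does. At this size, the fixed sequence still costs less power than an equal split over three contrasts (about 30–35%).
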